## Abstract

Background

Down syndrome (DS) is one of the most common chromosomal anomalies, affecting a substantial number of newborns globally. Pediatric patients with DS face a range of health challenges, including complex and often underrecognized pain experiences. These children may exhibit atypical responses to pain, such as reduced verbal expression, behavioral changes (e.g., freezing), or lower pain thresholds, that can render conventional pain assessment strategies insufficient. Consequently, there is a critical need for multidimensional tools specifically tailored to the characteristics of this vulnerable population. This study aims to develop and validate a novel mixed-methods instrument - the ANDREAS tool - designed to accurately assess acute pain in children with DS by integrating behavioral observations with self-report measures, where feasible.

Methods

A mixed-methods approach will be employed to adapt a pain assessment scale suitable for children with DS, combining behavioral observations with self-reported measures when possible. Pain-related behaviors will be identified through an extensive literature review and focus group discussions involving researchers, parents, and healthcare professionals. Additional methodological components will include defined randomization procedures for participant selection, clear inclusion and exclusion criteria, a standardized venipuncture protocol to induce pain, and a tailored training program for assessors to ensure methodological rigor. The resulting instrument, ANDREAS, will undergo validation using exploratory factor analysis and internal consistency testing (Cronbach’s alpha).

Results

The study is expected to yield a validated tool capable of capturing both the presence and severity of acute pain in pediatric patients with DS. Key behavioral indicators, such as freezing, defined as the absence of movement for at least five seconds during a painful stimulus, will be operationalized and assessed using a structured 0-4 rating scale. The integration of behavioral and self-report data is anticipated to enhance the sensitivity and specificity of pain detection in this population.

Conclusions

The ANDREAS instrument is expected to provide a reliable, valid, and clinically meaningful method for assessing acute pain in children with DS. By combining behavioral observations with self-report, it introduces a novel, multidimensional approach that may improve the accuracy of pain evaluation and inform more effective clinical management strategies. Future research will focus on further validating the instrument’s psychometric properties and exploring its use across diverse clinical settings.

## Introduction

Down syndrome (DS) is the most common chromosomal anomaly [1], affecting approximately one in every 640 newborns [2]. It is characterized by the presence of an extra chromosome, which leads to atypical psychophysical development and associated disabilities. Individuals with DS often face numerous health complications due to multiple comorbidities, frequently requiring medical interventions, surgical procedures, and hospitalizations. As a result, they experience pain more often than their typically developing peers [3].

Children with DS are known to have a lower pain perception threshold [4], reduced pain tolerance, delayed reaction times, prolonged pain experiences, and altered nociceptive signal conduction and modulation [5,6]. Moreover, their expression of pain is often ambiguous and challenging to interpret, both qualitatively and quantitatively [7]. Verbal responses and crying may be minimal or absent, while facial expressions tend to remain evident [8,9], sometimes accompanied by immobility of the face and body. This response pattern, known as “freezing,” refers to a paralytic reaction that may give the false impression of pain insensitivity.

Recent studies focusing on facial expressions provide promising insights into understanding pain in this population. Careful observation of facial cues may help clinicians detect pain without being influenced by the patient’s cognitive abilities. Additionally, the pain experience in individuals with DS can vary greatly due to heterogeneous structural and functional alterations in the central nervous system, which affect the transduction, transmission, modulation, and perception of sensory information [10].

Pain recognition is further complicated by subtle or idiosyncratic behaviors and wide individual variability in physical and expressive abilities, which are closely tied to different levels of cognitive development. Although self-report remains the gold standard for pain assessment, it is often difficult to apply and interpret in individuals with intellectual disabilities [5]. Children with such disabilities face considerable disparities in pain-related care and remain significantly underrepresented in pain research. Standard pain assessment tools are frequently inadequate for this population, especially for those who are nonverbal or unable to understand and follow instructions [11].

Importantly, children with DS are not insensitive to pain; rather, they tend to express discomfort more slowly and less clearly than their typically developing peers. This underscores the importance of implementing proactive pain management strategies, even in the absence of obvious pain cues. Despite this, current research appears insufficient in addressing the healthcare needs of this vulnerable group [12].

Therefore, it is a critical priority to develop assessment tools specifically designed to evaluate pain in children with DS and other forms of intellectual disability. The primary aim of this study protocol is to develop and validate a psychometrically robust, mixed-method instrument - ANDREAS - capable of accurately detecting and measuring the presence and intensity of pain in pediatric patients with DS. A secondary aim is to identify behavioral indicators of pain in relation to varying degrees of intellectual impairment.

## Materials and methods

Research hypothesis

Current pain assessment tools are not sufficiently specific, valid, or reliable for accurately measuring pain in children with DS.

Study objectives

The primary objective of this study protocol is to design and validate a reliable mixed-method assessment tool that incorporates both self-report and hetero-evaluation by healthcare professionals and family caregivers to accurately detect and measure pain in the pediatric population with DS. A secondary objective is to identify behaviors specifically indicative of pain in children with DS, according to their degree of intellectual disability.

Study design

This study adopts a single-center, observational, mixed-method design that integrates both qualitative and quantitative methodologies. The qualitative phase will involve a focus group with parents of children and adolescents with DS [13]. Semi-structured interviews, consisting of seven ad hoc questions (Table 1), will be audio-recorded, transcribed verbatim, and analyzed thematically. All qualitative procedures will adhere to the Consolidated Criteria for Reporting Qualitative Research (COREQ) [14].

**Table 1 TAB1:** Questions for the qualitative research DS, Down syndrome

Questions for a qualitative study addressed to parents of children with DS
Experience: Can you describe a specific time or situation when you recognized that your child was experiencing pain?
Facilitating factors: What signs or behaviors have helped you understand that your child was in pain? (How does your child communicate pain? Does your child use words, gestures, or other forms of expression? What kinds of verbal or nonverbal signs do you observe when your child is in pain?)
Hindering factors: What challenges have you faced in recognizing pain in your child? (Do you believe there are behaviors typical of DS syndrome that complicate pain recognition?)
Experience with healthcare professionals: What aspects of communication with healthcare professionals have you found most helpful or least helpful regarding your child’s pain?
Suggestion: Is there anything else you would like to share regarding your child’s experience of pain that we have not discussed so far? What advice would you offer to other parents who are facing similar situations?
Facilitating factors: What factors do you believe contribute to reducing your child’s perception of pain? (What elements help make the experience less traumatic?)
Relational question: How would you describe your emotional reactions as a parent when coping with your child’s pain?

Study procedures

The study will be conducted in five distinct phases. The first phase will focus on the development of an adapted “faces” pain assessment tool specifically designed for pediatric patients with DS. A body diagram for pain localization may also be incorporated. The tool will retain a self-report function to capture the pain experience directly from the young patients.

In the second phase, pain-related behaviors will be identified through structured interviews with professional caregivers (e.g., nurses, physicians, and psychologists). Caregivers will assess 12 predefined behaviors, drawn from established observational tools (e.g., brow lowering, eye squeezing, nasolabial furrow, and finger splaying), indicating whether they have observed each behavior during venipuncture procedures in children with DS. Each behavior will be marked as “observed” or “not observed.” Simultaneously, caregivers will complete an adapted six-face pain scale tailored for pediatric patients with DS, with two illustration sets (one featuring a child with glasses and one without) to accommodate visual aid preferences. The face that best represents the child’s pain intensity at the time of venipuncture will be selected. Data collected during this phase will contribute to refining the behavioral indicators included in the ANDREAS tool.

The third phase will further explore pain-related behaviors through a focus group involving parents. Using qualitative methods, parents will provide insights into their children’s pain expressions, offering a deeper understanding of individual variability.

Based on input from healthcare professionals and parents, the fourth phase will involve finalizing the list of items and measurement scales for the ANDREAS instrument. The tool will then undergo validation, with particular focus on its psychometric properties. An observational study will assess face, content, and construct validity through exploratory factor analysis (EFA), as well as evaluate reliability.

In the fifth and final phase, a comprehensive report will be prepared, and the results will be disseminated through publication. These findings aim to improve pain assessment practices for children with DS, enabling more accurate and individualized clinical interventions.

Each study phase involves specific procedures and participant groups, selected according to the phase’s objectives. Inclusion and exclusion criteria will be defined separately for the qualitative and quantitative components. The expected study duration is approximately 18 months, covering recruitment, data collection, and validation.

Qualitative study sample

The qualitative sample will consist of approximately 30 parents of children and adolescents with DS, chosen to reflect a range of ages and comorbidities while maintaining comparable levels of cognitive impairment. This sample size is based on evidence that 99.3% of concepts, themes, and content typically emerge after about 30 interviews [15]. Recruitment will continue until data saturation is reached [16].

Inclusion criteria include parents of children or adolescents with DS who present with mild to moderate-severe cognitive impairment, regardless of clinical condition. Participants must provide written informed consent and agree to participate in focus groups.

Exclusion criteria include parents who are unable to actively participate due to medical or psychological conditions, those whose children do not consent to the study, or those whose children’s cognitive impairments and pain-related behaviors are too complex to assess reliably.

Quantitative study sample and eligibility criteria

The sample size for the observational study is based on a hypothesized prevalence of pain in the pediatric DS population of approximately 30% [10], with a 95% confidence level and a margin of error of 7%. The standard formula for estimating sample size in prevalence studies is as follows:

\[n = \frac{Z^2 \cdot p \cdot (1 - p)}{d^2},\]

where Z = 1.96 (for 95% confidence), p = 0.30, and d = 0.07.

The resulting estimated sample size is approximately 165 child participants. All pediatric subjects whose parents provide informed consent will be eligible for inclusion.

Inclusion Criteria

Eligible participants will be children older than eight years whose parents voluntarily agree to enroll them in the study. This cohort will include children whose parents participate in the initial focus group as well as those involved in testing the newly developed pain assessment tool. Instrument testing will take place in healthcare facilities during venipuncture procedures in order to evaluate the tool’s capacity to detect the presence and intensity of pain.

Exclusion Criteria

Children will be excluded if their parents do not provide, or are unable to provide, informed consent. Additionally, any child with profound cognitive impairments that preclude reliable pain assessment will be excluded.

Variables to be collected

Audio recorders will be used to capture the focus group discussions and interviews. A specifically developed pain measurement tool will be employed to convert parental reports into coded data for further analysis.

Parent-related variables will include the parents’ age, sex, and educational background, as well as the number of years they have spent as caregivers or in direct care of their child. Information will also be gathered on the presence of other children in the family, the number of hospitalizations the child has undergone, and the reasons for these hospitalizations. Parents will be asked to describe their observations of their child’s experiences during pain episodes, including any distinctive behaviors exhibited during such episodes. Additionally, the impact of the child’s pain on family life, education, and learning will be documented.

Child-related variables will encompass the child’s age (restricted to those older than 8 years), gender, and current school grade. The child’s level of cognitive development will be assessed using the Leiter International Performance Scale, Third Edition (Leiter-3) [17]. The Leiter-3 is a standardized instrument designed to measure intelligence quotient (IQ) and cognitive ability in individuals aged three to over 75 years. Unlike conventional IQ tests, it focuses on fluid, nonverbal reasoning skills, making it especially suitable for individuals with cognitive or communication difficulties, including those with brain injuries or neurodegenerative conditions such as Alzheimer’s disease, Parkinson’s disease, or dementia.

Operationalization of the ANDREAS tool items

The ANDREAS tool will consist of observational items designed to capture specific behavioral indicators of pain in children with DS. Each item will follow a standardized structure and will be rated using a 5-point Likert scale (0 = never, 4 = always), based on either direct observation or caregiver report. Table 2 provides illustrative examples of item structure, behavioral domains, and the scoring criteria applied in the ANDREAS tool. The items will be organized into thematic domains such as facial expression, vocal behavior, and motor response. Their formulation will be grounded in qualitative findings derived from interviews and focus groups. To ensure consistent administration and interpretation, a coding manual containing operational definitions and detailed scoring guidelines will accompany the tool.

**Table 2 TAB2:** Examples of observational items included in the ANDREAS tool

Item example	Behavioral domain	Operational definition	Scoring scale
The child vocalizes through crying, moaning, or atypical sounds not attributable to known communicative patterns.	Vocal expression	Nonpurposeful vocalizations that occur in conjunction with observable signs of distress.	0 = never; 1 = rarely; 2 = sometimes; 3 = often; 4 = always
The child suddenly becomes immobile or assumes a rigid posture during a painful episode.	Motor behavior	A sudden cessation of voluntary movement lasting at least five seconds, not explained by external environmental stimuli.	0 = never; 1 = rarely; 2 = sometimes; 3 = often; 4 = always

Item development will follow an iterative, expert-led process involving multiple rounds of refinement, peer review, and pilot testing. This approach is intended to ensure that the tool remains closely aligned with the theoretical framework of pediatric pain in children with DS while also minimizing the risk of construct drift or item overfitting during the scale development process.

Training and standardization procedures

Prior to data collection, all researchers and healthcare professionals responsible for administering the ANDREAS tool will participate in a standardized training program. This program will include theoretical instruction, practical simulations using case studies, and the review of annotated video recordings. Training will focus on ensuring consistent interpretation of items, accurate scoring, and reliable behavioral observation techniques. Inter-rater reliability will be evaluated during pilot testing by calculating agreement levels using Cohen’s kappa coefficient.

Behavioral coding protocol

Each behavioral indicator included in the ANDREAS tool will be operationally defined within a structured coding manual. This manual will outline detailed criteria for identifying and rating observable pain-related behaviors. For example, “freezing” will be defined as the sudden cessation of voluntary movement lasting at least five seconds, unrelated to any external stimulus. Depending on the item format, each behavior will be rated either using a binary presence/absence code or a 5-point Likert scale (0 = never, 4 = always). All data will be initially recorded on paper forms and then transcribed into a secure, GDPR-compliant digital platform for managing sensitive health information. Specific coding protocols will be uniformly applied across all cases to ensure the accuracy, reproducibility, and traceability of behavioral observations.

Statistical analysis

Descriptive statistics will be used to characterize the study population, including measures such as means, standard deviations, medians, interquartile ranges, proportions, and correlation coefficients. Summary tables will present key sociodemographic and clinical variables, including sex, age, pain localization, duration, and intensity, along with their respective ranges.

Psychometric validation of the ANDREAS instrument will proceed in multiple stages. Construct validity will be assessed through EFA, depending on data characteristics and sample size. Prior to EFA, the suitability of the dataset will be determined using the Kaiser-Meyer-Olkin measure of sampling adequacy, with a threshold of ≥ 0.60, and Bartlett’s test of sphericity, with statistical significance set at p < 0.05. Factor extraction will be based on eigenvalues greater than 1 and scree plot inspection, with factor loadings of ≥ 0.40 considered acceptable.

Internal consistency will be evaluated using Cronbach’s alpha, with coefficients of ≥ 0.70 interpreted as satisfactory. Additional confirmatory analyses may be conducted depending on the robustness of the data. All statistical analyses will be performed using appropriate and validated software tools.

Ethical considerations

In accordance with the Guidelines for the Classification and Conduct of Research Studies, all data will be processed in compliance with current Italian legislation (Art. 13 of Law 196/2003; D.M. 5 July 1997 guidelines; Legislative Decree 200/2007), as well as the ethical principles of the Declaration of Helsinki. Data collection will involve both parental interviews, following informed consent obtained from parents for themselves and their children, and observational methods involving the children. Anonymity and confidentiality will be strictly upheld, with all personal data handled according to the provisions of Italian privacy laws (DL 196/03). A confidential list linking participant identification codes to their identities will be maintained by the project coordinators at the Department of Health Promotion, Mother and Child Care, Internal Medicine and Medical Specialties (PROMISE), Università degli Studi di Palermo. The study protocol received approval from the Palermo 3 Ethics Committee (protocol number 163_03/04/2024).

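### No phase records how often the candidate behaviours occur without pain, so the plan cannot show that any of them is specifically indicative of pain

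*Protocol article*

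**What the plan says.** The Study objectives section states: "A secondary objective is to identify behaviors specifically indicative of pain in children with DS, according to their degree of intellectual disability". Study procedures gives the second phase the task of finding the behaviours: "In the second phase, pain-related behaviors will be identified through structured interviews with professional caregivers". These caregivers work through 12 predefined behaviours taken from existing observational tools, "indicating whether they have observed each behavior during venipuncture procedures in children with DS". The response is binary: "Each behavior will be marked as" observed or not observed. The same caregivers also complete a six-face scale: "The face that best represents the child’s pain intensity at the time of venipuncture will be selected". The use of the results is stated as follows: "Data collected during this phase will contribute to refining the behavioral indicators included in the ANDREAS tool".

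The third phase is a parent focus group. The fourth phase finalises the items and tests the tool, and under Inclusion Criteria that testing is again placed at venipuncture. The Statistical analysis section names descriptive statistics, exploratory factor analysis and Cronbach's alpha. Cohen's kappa is named for pilot testing. The Abstract says that combining behavioural and self-report data "is anticipated to enhance the sensitivity and specificity of pain detection in this population".

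**The concern.** Calling a behaviour specifically indicative of pain is a statement about two frequencies: how often it occurs with pain and how often without. The plan collects only the first, and collects it in a setting where pain, fear, restraint and unfamiliar handling coincide. A habitual behaviour, or one driven by procedural distress, can be marked observed as readily as one that appears only with the needle.

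The plan shows awareness of the problem. Its hypothesis faults current tools for lack of specificity, and Table 1 asks parents about behaviours typical of Down syndrome that make pain harder to recognise. Without a non-painful record, the secondary objective and the specificity expectation rest on judgement rather than data. The comparison is hard to recover once the second phase is complete.

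**Working it through.** **The plan's own figure.** The only computed figure is the observational study's sample size: n = Z² × p × (1 − p) / d² = 1.96² × 0.30 × 0.70 / 0.07² = 164.64, rounded up to 165. It reproduces and is not in dispute.

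**Where a non-pain frequency could come from.**

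| Source | Condition observed | Non-pain frequency recorded? |
|---|---|---|
| Phase 2 checklist | Venipuncture | No |
| Phase 2 face rating | Same venipuncture, same caregiver | No |
| Phase 3 parent focus group | Recounted pain experiences; one prompt on syndrome-typical behaviours | No, qualitative only |
| Phase 4 instrument testing | Venipuncture | No |
| Named analyses (descriptive statistics, factor analysis, alpha, kappa) | Data as collected | None contrasts painful with non-painful states |

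**Why one frequency is not enough.** Write Se for P(behaviour | pain) and b for P(behaviour | no pain). Then:

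- specificity = 1 − b
- positive likelihood ratio LR+ = Se / b
- positive predictive value PPV = Se × p / (Se × p + b × (1 − p))

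Phase 2 informs Se at best, treating every venipuncture as painful. It carries no information on b.

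**Illustration.** Assumed, not in the documents: Se = 0.80, with b ranging from 0.05 to 0.80. For p, the 30% of the sample-size section is borrowed. That figure is a prevalence of pain in the population, not a rate at venipuncture.

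| b (unrecorded) | Specificity | LR+ | PPV at p = 0.30 |
|---|---|---|---|
| 0.05 | 0.95 | 16.0 | 0.87 |
| 0.20 | 0.80 | 4.0 | 0.63 |
| 0.40 | 0.60 | 2.0 | 0.46 |
| 0.60 | 0.40 | 1.33 | 0.36 |
| 0.80 | 0.20 | 1.0 | 0.30 |

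First row: LR+ = 0.80 / 0.05 = 16.0, and PPV = 0.24 / (0.24 + 0.035) = 0.87. In the last row PPV equals the assumed prevalence, so the behaviour says nothing about pain. All five rows would give the same expected Phase 2 result.

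**Sample size does not help.** With 165 observations, an 80% frequency has a 95% half-width of 1.96 × √(0.80 × 0.20 / 165) = 0.061. More children narrow this interval around Se and leave b unknown.

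**The case against.** The strongest defence is that the second phase is only a screening step. Its data contribute to refining the indicators. Items are finalised with parents' input, and then pass through iterative expert review, pilot testing and a factor-loading criterion of 0.40. Table 2's definitions already exclude known communicative sounds and immobility explained by the surroundings. The face rating gives a contrast between more and less painful venipunctures. The article also condenses a fuller protocol.

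Much of this stands, and it rules out stronger readings. A reader might infer that items enter the tool on sensitivity alone, or that behaviours common at venipuncture will be preferred to rarer, more specific ones. The document states no such rule. Nor is the abstract's specificity sentence a claim about Phase 2. It is an expectation for the whole tool, from combining behavioural and self-report data.

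The wording of the objective also leaves room. 'Specifically' could mean particular to children with Down syndrome at a given level of impairment, and the Introduction states the same aim without that word. Even so, a behaviour that indicates pain must be more frequent with pain than without it.

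None of these safeguards supplies the missing frequency. The face rating comes from the same caregiver at the same moment, so it is not an independent reference. Every rated child is undergoing the same procedure, and no analysis relating behaviours to faces is described. Condensation does not answer the point either, because the article states the observation condition for both phases, and an analysis plan cannot recover data that were not collected.

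**Conclusion.** The point holds in a limited form. As described, the second phase can list behaviours seen during a painful procedure, but neither it nor any later phase can show that a behaviour is specific to pain, because no non-painful observation is recorded. This affects the secondary objective and the specificity expectation in the Abstract. It does not affect the sample size, the factor analysis or the reliability assessment.

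The size cannot be computed from the documents. The LR+ range of 16.0 to 1.0 rests on assumed rates and shows only how much is left undetermined. The conclusion assumes that the full protocol has no non-painful record that the article leaves out, and that the objective is read as requiring a behaviour to distinguish pain from its absence.

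**What to change.** Add a second observed/not observed column to the same 12-behaviour checklist for a non-painful moment. If the form is completed for an individual child, use that child before the needle, ideally also during non-painful handling such as positioning or holding before needle insertion. A moment before the procedure is preferable to one after it, since the Introduction describes delayed reactions and prolonged pain in these children. If the second phase is a recall interview across patients, which the wording allows, ask about a recalled non-painful contact and treat the answer as weaker evidence.

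Use the difference between columns as one input, alongside parents' and experts' views, when items are finalised in the fourth phase. State the limit: a pre-procedure baseline screens out habitual behaviours but only partly separates fear or restraint distress from pain. Observing handling before insertion narrows that gap without closing it.

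The cost is one column and a little more of the professional's time per form.

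If no comparison is added, reword the objective to behaviours observed during a painful procedure, and remove the specificity expectation from the Abstract.

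### Face and content validity are assigned to factor analysis, and no named comparison or criterion ties the ANDREAS score to pain

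*Protocol article*

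**What the plan says.** All references are to the protocol article.

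- **Introduction, primary aim:** an instrument "capable of accurately detecting and measuring the presence and intensity of pain in pediatric patients with DS".
- **Study procedures, fourth phase:** the validation study is to "assess face, content, and construct validity through exploratory factor analysis (EFA), as well as evaluate reliability".
- **Abstract, Methods:** the instrument "will undergo validation using exploratory factor analysis and internal consistency testing", the latter by Cronbach's alpha.
- **Inclusion Criteria:** the instrument is tested at venipuncture, and the purpose given is to judge its "capacity to detect the presence and intensity of pain".
- **Statistical analysis:** construct validity, and only construct validity, is assigned to EFA. The criteria are KMO at least 0.60, Bartlett p below 0.05, eigenvalues above 1 with a scree plot, loadings at least 0.40 and alpha at least 0.70. Further confirmatory analyses are optional and unspecified.
- **Training and standardization procedures:** Cohen's kappa for rater agreement in pilot testing.
- **Abstract, Results:** combining behavioural and self-report data is "anticipated to enhance the sensitivity and specificity of pain detection in this population".
- **Research hypothesis:** "Current pain assessment tools are not sufficiently specific, valid, or reliable for accurately measuring pain in children with DS".

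**The concern.** Two statements do not fit the methods attached to them.

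First, face and content validity are judgements about clarity, relevance and coverage. EFA takes a correlation matrix as input and carries no information on any of these. The sentence in Study procedures is therefore wrong as written, and it disagrees with the Statistical analysis section.

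Second, the stated purpose of testing is to see whether the tool detects pain and grades its intensity. Detection needs a contrast between painful and non-painful states, or a reference rating. Intensity needs an external measure to set the score against. The article names neither, and its numerical criteria look only inward, at how the items relate to each other.

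A scale of general distress, fear or temperament could therefore meet every stated criterion and be reported as valid for pain. The Conclusions foresee use in clinical and home settings, so such a result would be acted on. If no pre-procedure rating is made at the visit, it cannot be recovered later.

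**Working it through.** **1. The plan's own figure.** Quantitative study sample section: Z = 1.96, p = 0.30, d = 0.07.

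n = Z²p(1−p)/d² = 3.8416 × 0.21 / 0.0049 = 164.64, rounded up to 165. The stated size reproduces and is not disputed here.

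**2. Which property each planned method can address.**

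| Method in the article | What it uses | What it can show |
|---|---|---|
| EFA, KMO, Bartlett, loadings | Inter-item correlations | Dimensionality |
| Cronbach's alpha | Inter-item covariances | Internal consistency |
| Cohen's kappa (pilot) | Paired raters | Rater agreement |

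None of these addresses face or content validity, or relates the score to pain.

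**3. Can a score unrelated to pain meet the criteria?** This was simulated with 1000 runs per scenario and n = 165. The following assumptions are not in the article: 12 items scored 0 to 4, one common factor with loading 0.65, and the 30% of children with the highest true pain labelled as in pain. Loadings were taken from the first principal component. The correlation between the common factor and true pain was set to 0.9, 0.5 or 0.

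| Factor–pain correlation | Mean alpha | Mean KMO | Alpha, KMO and Bartlett criteria each met | All loadings at least 0.40 | Mean correlation of score with pain | Mean AUC for pain |
|---|---|---|---|---|---|---|
| 0.9 | 0.88 | 0.92 | 100% | at least 99.9% | 0.84 | 0.91 |
| 0.5 | 0.88 | 0.92 | 100% | at least 99.9% | 0.47 | 0.72 |
| 0 | 0.88 | 0.92 | 100% | at least 99.9% | 0.00 | 0.50 |

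Alpha and KMO do not change across the rows, because they depend only on how the items relate to each other. The item count and loading affect their level, not this invariance.

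**4. What 165 children would support if an external comparison were added.**

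- Correlation of the behavioural total with a faces rating, taking r = 0.50 as an illustration: Fisher z = 0.549, standard error 1/√162 = 0.0786, limits 0.549 ± 0.154. Back-transformed, the 95% CI is 0.38 to 0.61.
- Paired change from before to during the procedure, 80% power, two-sided 5%: (1.96 + 0.842)/√165 = 0.218 SD of the paired differences.

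These two figures describe the remedy, not the size of the defect.

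**The case against.** The strongest reply is that the Study procedures sentence is loose wording in a condensed article. The Statistical analysis section has it right. Material bearing on content validity is planned: interviews with professionals, a parent focus group, expert-led refinement, peer review and pilot testing. Convergent-validity detail commonly sits in an analysis plan that is not shown. Much of this stands. The first part needs only a corrected sentence plus a stated way of using those inputs, and the absence of a listed correlation would not be a finding by itself. What remains is a purpose stated in the article that the methods and criteria stated in the same article cannot serve.

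A reader might infer more, and the article does not support it:

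- **That there will be no non-pain observations, so specificity cannot be estimated.** The article gives the setting of testing, not the timing of every rating, and the standardized venipuncture protocol mentioned in the Abstract is not detailed. The supportable statement is that no non-painful comparison is named.
- **That sensitivity and specificity are endpoints left without an analysis.** They appear only as an expected benefit in the Abstract, not in the objectives or the Statistical analysis section.
- **That the hypothesis requires scoring existing tools alongside.** It reads as rationale. The objectives concern developing and validating ANDREAS, so rewording is enough.
- **That a quiet-baseline AUC would settle the matter.** Fear, restraint and distress change together with pain, and a rater who knows which period is being scored may expect a difference. A pure fear scale could do well on it. The freezing item also presupposes a painful episode, so it cannot be scored beforehand as worded.

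**Conclusion.** The point holds in a limited form. The Study procedures section misassigns face and content validity to EFA and conflicts with the Statistical analysis section. The Inclusion Criteria section gives testing a purpose, detecting pain and its intensity, for which no contrast, reference rating or external criterion is named.

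The stated criteria do not fill that gap. Under the simulated conditions a score with zero correlation with pain met each of them in at least 99.9% of runs, with mean AUC 0.50. The exact percentages rest on the assumed 12 items and loading of 0.65. The conclusion rests only on the fact that these criteria use relations among the items. The claim is not that ANDREAS will fail to measure pain, but that passing the stated criteria would not show that it does.

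**What to change.** 1. Correct the fourth-phase sentence. Assess face and content validity by structured relevance and clarity ratings from the experts and parents already involved, and keep EFA for structure.
2. Prespecify the correlation of the behavioural total with the child's faces self-report, and with the proxy faces rating, at the same venipuncture. Name this as the convergent-validity analysis for intensity.
3. Add a same-visit pre-procedure rating with item wording neutral to pain, which means rewording the freezing item. Report the paired change as responsiveness to the procedure. State that it does not separate pain from fear and that the rater is not blinded.
4. If items 2 and 3 are not adopted, limit the conclusions to structure and internal consistency. Soften the Abstract's expectation on sensitivity and specificity, and reword the hypothesis so that it concerns ANDREAS.

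The cost is one more short rating per child, a relevance and clarity form, some item rewording and a few correlations. The sample size need not change for this point. The changes should be made before data collection.
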